**Fig. 1 Fig1:**
[figure not shown]
Expected trial plan. Not included in the diagram are excluded participants that may stop participation at any time during weeks 0–12 due to various reasons including failure to meet inclusion criteria or inability to continue at-home intervention. The intervention tasks are 25 min total, with two 10-min sets with a 5-min break between each set

**Fig. 2 Fig2:**
[figure not shown]
Standard Protocol Items: Recommendation for Interventional Trials (SPIRIT). W, weeks; SFT, synchronous finger tapping; HC, healthy control; CFT, continuous finger tapping; fNIRS, functional near-infrared spectroscopy; MoCA, Montreal Cognitive Assessment Test; UPDRS, Unified Parkinson’s Disease Rating Scale

### Sample size {14}

For this study, a total 210 participants (70 participants in three groups with a 10% attrition rate), are recruited over an 18-month period. We aim to recruit an even distribution of age, PD staged I, and II as determined by the Hoehn and Yahr scale, and gender to maximize statistical significance. This study is an exploratory prospective randomized controlled study with the primary outcome being the HbO_2_ value measured by fNIRS. Because there are no pilot study nor previous studies identical to this, the sample size was calculated by using power calculations (where *α* = 0.05, *β* = 80%, and we assume a conservative average difference between the PD groups). Klempir et al.’s study was used to estimate the baseline averages of HbO_2_ changes; however, there are notable inherent differences between this protocol and the referenced study. Klempir et al. describes HbO_2_ changes between participants with and without DBS during a finger tapping exercise [34]. Although our study may involve participants who use DBS as a treatment, we are not examining how various forms of treatment (pharmaceutical or DBS) affect motor control. Thus, the estimated HbO_2_ baselines when DBS is ON from Klempir’s study were approximations of the PD control group’s performance.

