#### fNIRS data

An initial band pass filter will be applied to the raw fNIRS data before further processing to remove noise and drifts. Neuroactivity in various regions of interest including, prefrontal, pre-motor, supplementary, and primary cortex, will be analyzed by constructing a general linear model for each subject then estimating parameters and obtaining contrast values of the total oxy-Hb and deoxy-Hb signals. The contrast value images can be averaged within groups and a group analysis can be done using a *t* test. The averaged signal levels of each group will be plotted on a time vs total blood flow graph and compared to determine intervention effect.

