### Methods in analysis to handle protocol non-adherence and any statistical methods to handle missing data {20c}

Missing data and any data collected not adhering to the protocols will be removed from data analysis.

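### The sample-size statement gives β as 80%, which is literally 20% power; 80% power is very probably meant, but 70 per arm fits either reading, and the rule removing non-adherent data could cut power further

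*Protocol article*

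**What the plan says.** All references are to the protocol article.

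- **Size.** Sample size {14} plans for "a total 210 participants (70 participants in three groups with a 10% attrition rate), are recruited over an 18-month period". Concealment mechanism {16b} numbers participants from 1 to 210, so 70 per group is the number recruited. Sequence generation {16a} randomises the PD participants 1:1.
- **Basis.** The same Sample size section names one outcome, "with the primary outcome being the HbO_2_ value measured by fNIRS", sets α at 0.05 and gives "β* = 80%, and we assume a conservative average difference between the PD groups". It attaches no value to that difference. A cited study of finger tapping with and without deep brain stimulation "was used to estimate the baseline averages of HbO_2_ changes".
- **Test.** The fNIRS data section says that "a group analysis can be done using a *t* test". It does not say whether the test is one- or two-sided.
- **Losses.** Recruitment {15} puts attrition at 10%, covering withdrawal, illness and other uncontrolled factors.
- **Removal of data.** Section {20c} says: "Missing data and any data collected not adhering to the protocols will be removed from data analysis".
- **Retention of data.** Explanation for the choice of comparators {6b} says that departures from the PD controls' baseline care are recorded and included in the analysis. The section on communicating amendments {25} says that data from protocol deviations are marked and considered in the analysis.

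**The concern.** The quantity normally given beside α is either power (80%) or β (20%). The article attaches the value of one to the symbol of the other. A slip of this kind is harmless when the other inputs allow the reader to rebuild the calculation. Here they do not, and the stated sample size agrees with both readings. A reader of a null result on HbO2 could not tell whether the trial was planned to find a medium difference with good power or a small one with poor power.

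The removal rule raises a second question about the same planning figure. The training is daily, at home, for 8 weeks, and video-monitored. Under Strategies to improve adherence {11c}, videos from the intervention arm are scored for adherence and accuracy, while the control arm gets only a binary adherence score. Removing non-adherent data may therefore take more from one arm than the other. That lowers power, and it compares groups no longer formed by randomisation alone.

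**Working it through.** **Inputs.** From the article: α = 0.05; 70 recruited per PD arm; 1:1 allocation; 10% attrition; a *t* test. Assumed here: a two-sided test, because no sidedness is stated. The difference and SD are not given, so the stated 70 cannot be reproduced forwards. I solve backwards for the standardised difference d (difference divided by SD).

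**Step 1: retained size.** 70 × 0.9 = 63 per PD arm.

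**Step 2: detectable difference.** For two means with n per arm, d = (z for two-sided α + z for power) × √(2/n), and √(2/63) = 0.178.

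| Reading of the 80% | Sum of z values | d at 63 per arm | *t*-test check |
|---|---|---|---|
| Power 80% (β = 20%) | 1.960 + 0.842 = 2.802 | 0.499 | 0.503 |
| β = 80% (power 20%) | 1.960 − 0.842 = 1.118 | 0.199 | 0.200 |

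If the test were one-sided, the two values of d would be 0.443 and 0.143.

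**Step 3: forward check.** n per arm = 2 × (sum of z values)² / d².

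- d = 0.5, power 80%: 2 × 2.802² / 0.25 = 62.8, so 63; 63 / 0.9 = 70. This is the stated figure. The *t* test gives 64, or 72 after inflation.
- d = 0.2, power 20%: 2 × 1.118² / 0.04 = 62.5, so 63; 63 / 0.9 = 70. This is also the stated figure.
- d = 0.2, power 80%: 393 per arm, or 437 with 10% attrition.

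Both readings return exactly 70, under different unstated differences.

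**Step 4: power that 63 per arm delivers (two-sided 0.05, normal approximation).**

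| True difference (SD) | Power |
|---|---|
| 0.2 | 20% |
| 0.3 | 39% |
| 0.4 | 61% |
| 0.5 | 80% (79.5% by the *t* test) |

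**Step 5: effect of removing data.** The article gives no removal rate. As an illustration only, take a further 20% or 30% out of the 63 in the intervention arm and leave the control arm at 63.

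- 63 × 0.8 = 50: 50 against 63 at d = 0.5 gives 74% (*t* test).
- 63 × 0.7 = 44: 44 against 63 at d = 0.5 gives 71% (*t* test).

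**Step 6: the handling rules side by side.** Section {20c} removes data that do not adhere to the protocol. Section {25} keeps data from protocol deviations, marked, and section {6b} keeps departures from baseline care in the analysis. The same record could be removed under the first rule and retained under the others.

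**The case against.** The strongest reply is that this is a slip in a symbol. A medium difference of 0.5 SD with 80% power and 10% attrition gives exactly 70 per arm, 3 × 70 = 210 matches the numbering in {16b}, and 80% is the conventional target for power. I accept that 80% power is very probably what was meant. The reply does not close the matter, because the literal reading reproduces 70 equally well.

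The article may also leave the difference and SD to the full protocol. That stands, and their absence is not in itself the complaint. They are needed here only because they are what would resolve a misstatement that the article does contain.

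On losses, the 10% explicitly includes other uncontrolled factors, no passage gives a non-adherence rate, and sections {6b} and {25} point towards keeping the data. Section {20c} could also be read narrowly, as covering only assessments collected off-protocol. So loss beyond 10% is a risk, not a demonstrated error.

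Three stronger readings are tempting, and the documents do not support them:

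- **That the trial is under-recruited.** If 70 were the evaluable target, 70 / 0.9 = 77.8, so 78 per arm and 234 in all would be needed. But {14} describes 70 per group as recruited and {16b} stops at 210, so the text contradicts nothing here.
- **That power must be computed with α split over the several primary outcomes in Outcomes {12}.** The trial is sized on one outcome, HbO2, is called exploratory, and nowhere splits α. Any reduced power on that ground would rest on an adjustment that the plan does not make.
- **That the trial's power has been shown to be 20%, or otherwise inadequate.** Only the label is shown to be wrong. The real power is unknown.

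**Conclusion.** The value given for β is wrong as written under the usual definition. The consequence is limited but real: planned power cannot be verified, because 63 retained per PD arm corresponds to about 0.50 SD at 80% power or about 0.20 SD at 20% power. This rests on a two-sided test and 10% attrition. The 0.50 SD is solved back from the sample size and must not be taken as the design assumption.

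The removal rule in {20c} is a separate, stated defect. It conflicts with {6b} and {25}, and it can both shrink and bias the randomised comparison. Its cost in power is conditional: from about 80% to 74–71% at 0.50 SD, if a further 20–30% of the intervention arm were removed. Those rates are assumptions.

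**What to change.** 1. In Sample size {14}, replace the β figure with power 80% (β = 20%), two-sided α = 0.05, 70 randomised and 63 expected evaluable per PD arm. The sponsor should confirm that this, including the sidedness, is what the calculation used.
2. Confirm the HbO2 difference and SD actually used. If they imply less than about 0.50 SD, state the power that 63 per arm delivers, from the table in step 4. Do not insert 0.50 SD merely because it fits.
3. In {20c}, replace the removal of non-adherent data with a primary comparison of all randomised PD participants who have outcome data, in the group to which they were assigned. Keep deviations flagged, as {25} already provides, and use the flags in a sensitivity analysis. This also brings {20c} into line with {6b} and {25}.

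The cost is wording and one analysis rule. Enrolment does not increase. The stated power may look less favourable if the assumed difference proves to be small.

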## Interventions

### Explanation for the choice of comparators {6b}

The PD intervention group is compared with the PD control group and a healthy control (HC) group. The PD control group is composed of participants diagnosed with PD and who meet the inclusion criteria. This PD control group is instructed to maintain the participants’ prescribed medication and care documented at the time of baseline assessment including any form of deep brain stimulation, if applicable. Any deviation from what was recorded at the time of taking baseline assessments are recorded during assessments and included when analyzing the data.

The second control group, the HCs, is composed of participants who meet the HC group inclusion criteria. This group predominantly consists of healthy spouses of the PD participants and individuals who share similar demographics to the participants diagnosed with PD. Measurements from the HCs are necessary because they serve as a normal, non-pathological benchmark, which has not been recorded before with this specific demographic and type of study paradigm. Furthermore, since spouses typically have similar lifestyles as their partners the measurements taken may help reduce the uncontrollable deviations due to dietary habits, living conditions, and environmental factors. HCs are asked to continue normal routine and must report any major deviations from baseline assessment routine (e.g., new medication to treat non-neurological illnesses that may affect motor movement or major injuries like head trauma). These deviations are noted for data analysis.

The neuronal activities of generating motor movement or processing a rhythmic external cue each should separately elicit measurable neuronal activation. However, when combined, a sensorimotor integration effect occurs such that motor movement is the result of a rhythmic external cue. Thus, the use of the HC and PD controls is to examine how movement coupled with an external sensory cue (a rhythmic auditory stimulus and in this study, music with rich rhythmic contents) impacts motor synchronization and control in PD.

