## Assignment of interventions: allocation

### Sequence generation {16a}

Participants with PD are sorted into and then randomized into the intervention or control groups in a 1:1 balanced ratio stratified by gender and PD staged I and staged II as determined by the Hoehn and Yahr scale. Allocation into randomized study groups are conducted via a computer-generated random number table and determined during the pre-study procedures during allocation when informed consent and baseline measurements are made. The number generation is facilitated by R3.6.3, a computer random number generator typically used by the Scientific Research Department of the hospital. Participant groups are not known to clinical investigators, site personnel, nor data analyzers.

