### Methods for additional analyses (e.g., subgroup analyses) {20b}

Further statistical analysis may be explored to account for interacting factors including gender, age, and different stages of PD as determined by the Hoehn and Yahr scale.

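### The control-arm HbO2 value comes from DBS-ON patients, but the PD arms may hold both DBS and non-DBS patients and the stated comparison ignores DBS status: a possible, unquantifiable loss of precision

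*Protocol article*

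**What the plan says.** All references are to the protocol article.

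- **Sample size {14}.** HbO2 is the outcome used for sizing. A cited study of finger tapping with and without DBS supplies the averages: the "study was used to estimate the baseline averages of HbO_2_ changes". The section grants that this study differs from the trial, says that DBS users might take part, states that forms of treatment are not being examined, and concludes that "the estimated HbO_2_ baselines when DBS is ON from Klempir’s study were approximations of the PD control group’s performance". For the contrast itself it says only "we assume a conservative average difference between the PD groups".
- **Eligibility criteria {10}** and **Relevant concomitant care {11d}.** Stable anti-PD dosing or stable DBS is acceptable. No expected or maximum DBS share is given.
- **Explanation for the choice of comparators {6b}.** PD controls keep the "care documented at the time of baseline assessment including any form of deep brain stimulation, if applicable". Deviations from that baseline regimen enter the analysis; baseline DBS status is not said to.
- **Sequence generation {16a}.** Allocation is in a "1:1 balanced ratio stratified by gender and PD staged I and staged II". DBS is not a stratum.
- **Statistical methods {20a}.** Tapping and neuropsychological measures are compared by a two-sample t test, and fNIRS contrast values by a t test on group averages. Neither has a DBS term.
- **Methods for additional analyses {20b}.** Optional further work may cover "interacting factors including gender, age, and different stages of PD". DBS is not named.

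**The concern.** The sizing rationale contains a step that does not hold. Deciding not to study DBS does not make a control arm of possibly mixed treatment resemble a DBS-ON group. It makes DBS a nuisance factor. The cited study contrasts HbO2 with and without DBS on a similar task, and one of its two conditions was chosen as the reference, so whether that condition represents the trial's controls needs a reason other than the one given.

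If DBS and non-DBS patients differ in the quantity analysed, an unadjusted t test puts that difference into the error variance. The PD intervention-versus-control contrast is then estimated less precisely than it could be, although the information needed to remove this variation is already documented at baseline.

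**Working it through.** **1. The plan's own figure.** The protocol states "a total 210 participants (70 participants in three groups with a 10% attrition rate" and says that "the sample size was calculated by using power calculations", with alpha 0.05 and a figure of 80% labelled beta, read here as power. It gives no difference, no SD and no sidedness, so 70 per group cannot be reproduced from its inputs. It can only be solved backwards, assuming a two-sided test:

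- Evaluable per arm: 70 × 0.9 = 63.
- Normal approximation: n = 2(z₀.₉₇₅ + z₀.₈₀)²/d². An assumed d = 0.5 gives 2 × 7.849/0.25 = 62.8, so 63, and 63/0.9 = 70.
- t test with 63 per arm: 80% power at d = 0.503.

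So 70 is consistent with a standardised difference of about 0.5, but the protocol does not state that value. It is an assumption in what follows.

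**2. Effect of mixing.** Let p be the DBS share in each arm and D the DBS versus non-DBS difference in the analysed quantity, in units of the SD within treatment type. Both are assumed, since the protocol gives neither. Then

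variance = 1 + p(1 − p)D², and the effective d = 0.503/√variance.

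Power of the two-sided t test with 63 per arm (80.0% without mixing):

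| p | D = 0.5 | D = 1.0 | D = 1.5 |
|---|---|---|---|
| 2% | 79.8% | 79.2% | 78.3% |
| 5% | 79.5% | 78.1% | 75.9% |
| 10% | 79.1% | 76.5% | 72.4% |
| 20% | 78.4% | 73.9% | 67.1% |
| 30% | 78.0% | 72.1% | 63.6% |

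Example: p = 0.10 and D = 1 give variance 1 + 0.09 = 1.09 and d = 0.503/√1.09 = 0.482, hence 76.5%. With p = 0.30 the variance is 1.21 and d = 0.457, hence 72.1%. At D = 1 the loss over p = 10-30% is therefore 80.0 − 76.5 = 3.5 to 80.0 − 72.1 = 7.9 points. At shares of 5% or below and D up to 1 it is 2 points or less.

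**3. What D refers to.** Outcomes {12} expresses the HbO2 outcome as reduction from baseline and derives outcomes from differences between time points, with DBS held stable. If DBS adds a constant b to a patient's HbO2 at every visit, the change score is (Y₈ + b) − (Y₀ + b) = Y₈ − Y₀, and b drops out. For a change-score analysis D is then the difference in mean *change* between DBS and non-DBS patients, and may be near zero even if levels differ. The table applies with a full level difference only if follow-up values are compared without reference to baseline.

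**4. Chance imbalance.** With 25 DBS users among 126 evaluable patients (about 20%), the hypergeometric probability that the arms differ by 10 or more percentage points in DBS share is 17.9%. At D = 1 a 10-point difference moves the contrast by 0.10 SD, against a standard error of √(2/63) = 0.178 SD, a ratio of 0.56. This is how the extra variance in step 2 reaches an unadjusted contrast. It must not be added as a second loss.

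**The case against.** A reader might infer that the sizing left this variation out and that the trial therefore falls short of 80% power. The documents do not support that. A control-arm mean does not determine N; the difference and the SD do, and neither is given. Nothing shows that the SD used was one from DBS-ON patients only.

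A reader might also infer that the arms do mix the two treatment types. The protocol says only that DBS users may be among the participants, and enrolment is limited to Hoehn and Yahr stages I and II. The share could be close to zero. Shifts of 1 or 1.5 SD have no basis in the protocol either, since it reports neither the direction nor the size of the cited study's DBS contrast.

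The change-from-baseline argument is the strongest, and much of it stands: under stable DBS a constant shift cancels. It does not settle the matter. Sample size {14} names the HbO2 value as the outcome, the fNIRS analysis text averages contrast values without saying that they are changes, and cancellation would not remove a response to training that differs by DBS status.

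Finally, the protocol concedes that the source study differs from the trial and calls the values approximations. The list of additional factors is open-ended, and covariates are often left to an analysis plan that is not shown. The absence of a DBS term is thus no defect by itself, and the unadjusted t test is not invalidated by ignoring DBS. What stands is the faulty inference in Sample size {14}, together with a stated comparison that leaves a documented baseline factor unused.

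**Conclusion.** The point holds in a limited form, at minor severity. The control-arm value comes from DBS-ON patients for a reason that does not justify it, the PD arms may contain both DBS and non-DBS patients, and DBS status is outside the strata and the stated t tests.

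The consequence is possible loss of precision. It is not bias: 1:1 randomisation balances DBS use in expectation, and chance imbalance is already part of the precision loss.

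The size cannot be determined from the protocol. It is negligible if few DBS users enrol or if a constant shift cancels in the change score. It is about 3 to 8 points of power if the share is 10-30% and the two types differ by 1 SD in the analysed quantity, assuming 63 evaluable per arm, a two-sided 5% t test and 80% power without mixing. A claim that the intended power has been lost would go beyond what the documents show.

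**What to change.** - **Analysis.** In the PD intervention-versus-control comparison of HbO2 change, prespecify baseline DBS status (yes/no) as a covariate, and add one sensitivity analysis excluding DBS users.
- **Sample size {14}.** State that the assumed control value comes from DBS-ON patients and may not represent a mixed control arm. Drop the inference that the value applies because treatment is not being studied. Do not state that 80% power holds for the adjusted analysis; without a difference and an SD that cannot be verified.

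Cost: one degree of freedom (123 instead of 124 residual degrees of freedom with 126 evaluable patients), one extra analysis and a few words of text. No new data are needed, because DBS is already documented at baseline. If few DBS users enrol, the gain will be small.

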### Recruitment {15}

Potential participants are recruited from the First Affiliated Hospital of Dalian Medical University. Recruitment will be managed by BZ and ZL. Participants’ spouses are also invited to participate as healthy controls if they meet the inclusion criteria. We will assume a conservative estimate of 10% attrition due to various reasons such as voluntary withdrawal, illnesses during studies, and other uncontrolled factors.

## Assignment of interventions: allocation

### Sequence generation {16a}

Participants with PD are sorted into and then randomized into the intervention or control groups in a 1:1 balanced ratio stratified by gender and PD staged I and staged II as determined by the Hoehn and Yahr scale. Allocation into randomized study groups are conducted via a computer-generated random number table and determined during the pre-study procedures during allocation when informed consent and baseline measurements are made. The number generation is facilitated by R3.6.3, a computer random number generator typically used by the Scientific Research Department of the hospital. Participant groups are not known to clinical investigators, site personnel, nor data analyzers.

